## Abstract

**Background:**

Individuals with autism spectrum disorder (ASD) often exhibit low dietary diversity due to food selectivity, leading to various forms of malnutrition, such as obesity or micronutrient deficiencies.

**Objective:**

The main objective of the AUT-MENU project is to improve meal acceptance among individuals with ASD. A secondary goal is to evaluate the effectiveness of a nutrition education course for parents of enrolled participants to reduce food selectivity.

**Methods:**

The study is a bicentric intervention conducted in 3 care centers (Pavia and Milan) and 1 secondary school (Rome), involving approximately 200 participants with ASD aged 3 to 35 years. The study consists of an observational phase (T0) and an intervention phase (T1). At T0, biographical data, clinical characteristics, and dietary patterns of participants are collected. Based on T0 findings and existing nutritional recommendations for individuals with ASD, targeted menus are developed and tested. At T1, the same assessment tools used at T0 will be applied to evaluate intervention effects. Additionally, a nutrition education course for caregivers will be implemented between T0 and T1, with a pre- and postcourse knowledge questionnaire to assess its effectiveness.

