#### Secondary Objectives

The secondary objective is to evaluate the feasibility of a structured nutrition and behavioral education program for parents and caregivers of enrolled participants. This intervention aims to improve parents’ knowledge on FS and meal experience at home, complementing the modifications implemented in the collective catering settings.

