#### Nutrition Education Course for Parents and Caregivers

Between the T0 and T1 phases, a digital nutrition education course will be offered to subgroups of parents and caregivers of enrolled participants in the Milan and Pavia centers. The course aims to reduce meal-related behavioral difficulties, including FS in individuals with ASD. Participation will be voluntary, following an informational session on the project’s objectives. Designed based on healthy eating guidelines and scientific literature on ASD and nutrition, the course is led by a multidisciplinary team, including a dietitian, nutrition biologists, speech therapists, and a psychologist. It consists of 7 modules delivered through weekly 1-hour sessions, integrating theoretical explanations with practical demonstrations using videos, images, and digital activities. The topics covered in the modules are as follows:

Module 1: the role of nutrition on health and macro- and micronutrients.Module 2: FS: associated factors and consequences.Module 3: healthy plate tailored to the needs of individuals with ASD.Module 4: behavioral strategies for the consumption of nonpreferred foods.Module 5: sensory strategies for the consumption of nonpreferred foods.Module 6: environment and meal presentation.Module 7: mother-child relationship.

To assess the course’s impact and feasibility, specific evaluation tools (detailed in the following section) will be used, along with the recording of attrition rates throughout the program.

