#### Nutrition Knowledge

Nutrition knowledge will be assessed in parents and caregivers participating in the nutrition education course. A questionnaire, designed based on the course topics, consists of 21 questions (3 per module; Multimedia Appendix 7). Researchers will administer the questionnaire via telephone interviews before and after the course to evaluate knowledge acquisition.

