### Outcomes and Statistical Analysis

The main outcome of the study testing the improvement of the meal acceptance is an increased food consumption of the proposed targeted meals. Specifically, food acceptance of targeted menus will be calculated as the average intake of the 12 administered set meals, ranging from 0 to 1, comparing results collected at T0 and at T1. The improved food acceptance associated with targeted menus will be estimated assuming a threshold of acceptance of 0.6, calculated as the percentage of cases showing an average PDAT lower than that value. Since the results of the pilot study were encouraging [6], showing an average PDAT greater than or equal to 0.8 in 50% (n=22) of participants, a threshold of 0.6 is assumed as a precautionary measure due to the variability in standard meal composition.

Multiple correspondence analysis at T0 was used to study the association between specific sensory aspects and food consumption, categorized into 5 levels (1=no consumption to 5=total consumption). The analysis produced a map showing the distances between the categories of the qualitative variables and food consumption levels.

Concerning the subgroup of caregivers attending the nutrition education course, statistical analysis will focus on effectiveness evaluation of the course, measured by the comparison of nutrition knowledge score, the prevalence of FS score, and the adherence to the Mediterranean diet score before and after the education intervention and by the dropout rate at the end of the course.

Since no preliminary information is available on the average consumption and variability of the PDAT, the determination of sample size is made on the expectation of a possible decreased propensity of FS. FS is an attitude found in 80% of the population with ASD, starting as early as childhood [6]. Hence, setting a significant level of α=.05 and a test power of 90%, under the assumption that the rate of FS may decrease to 15 percentage points, namely from p(T0)=80% to p(T1)=65%, 150 participants could be sufficient [22].

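### The course is meant to reduce food selectivity, but the only score scheduled both before and after it is a knowledge questionnaire written from its own modules

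*Protocol article*

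**What the plan says.** The Protocol article describes the purpose of the course in three places, and they differ.

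- Abstract, Objective: to "evaluate the effectiveness of a nutrition education course for parents of enrolled participants to reduce food selectivity".
- Secondary Objectives: to "evaluate the feasibility of a structured nutrition and behavioral education program for parents and caregivers of enrolled participants", with the intervention directed at parents' "knowledge on FS and meal experience at home".
- Nutrition Education Course for Parents and Caregivers: "The course aims to reduce meal-related behavioral difficulties, including FS in individuals with ASD".

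It also describes the measurement in several places.

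- Abstract, Methods: the course comes "with a pre- and postcourse knowledge questionnaire to assess its effectiveness". The same paragraph says "At T1, the same assessment tools used at T0 will be applied to evaluate intervention effects".
- Nutrition Knowledge: "A questionnaire, designed based on the course topics, consists of 21 questions (3 per module; Multimedia Appendix 7"). It is given by telephone before and after the course, and its stated use is to evaluate what caregivers have learned.
- Outcomes and Statistical Analysis: "effectiveness evaluation of the course, measured by the comparison of nutrition knowledge score". The sentence goes on to list the FS score, the Mediterranean diet score and the dropout rate.
- Table 1: BAMBI/STEP (FS) and KIDMED/MEDQS (Mediterranean diet) have a tick under T0 and an empty cell under T1. The sections Feeding Behaviors During Mealtime and Food Habits likewise describe them as assessed at T0.

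**The concern.** In the Abstract, effectiveness means less FS when the goal is set and a better questionnaire score when the assessment is named. These are different quantities in different people: FS belongs to the participant with autism, knowledge to the caregiver. A questionnaire with three items on each module can be expected to improve when people attend the modules and answer the items a second time, whether or not anything changes at the table.

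This would matter little if FS were also measured after the course. The analysis section implies that it will be; the schedule says that it will not. If the schedule is what was carried out, a statement that the course worked could be supported only by knowledge. Readers would take it as a statement about FS, because the Abstract defines the goal that way and Principal Findings anticipates a reduction in FS among participants whose caregivers attended.

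**Working it through.** No computed figure in the document bears on this point. The only one is the sample size of 150. It reproduces as a one-sided comparison of two independent proportions, 80% and 65%, at alpha 0.05 and 90% power: [1.645 × √(2 × 0.725 × 0.275) + 1.282 × √(0.8 × 0.2 + 0.65 × 0.35)]² / 0.15² ≈ 150 per group. It concerns the study as a whole and not the course, and is not used below.

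The check is a comparison of the effectiveness measures named in Outcomes and Statistical Analysis with their scheduled timing.

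| Measure | Before the course | After the course | Source of timing | Pre/post possible as scheduled |
|---|---|---|---|---|
| Knowledge questionnaire | yes | yes | Table 1; Nutrition Knowledge | yes |
| FS (BAMBI, STEP) | T0 | not scheduled | Table 1; Feeding Behaviors During Mealtime | no |
| Mediterranean diet (KIDMED, MEDQS) | T0 | not scheduled | Table 1; Food Habits | no |
| Dropout rate | not applicable | end of course | Outcomes and Statistical Analysis | not a pre/post score |

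1. Three scores are to be compared before and after the course: knowledge, FS and Mediterranean diet.
2. Scores with both time points in Table 1: one, knowledge. Scores with T0 only: 3 − 1 = 2.
3. Content of the remaining score: 7 modules × 3 questions = 21 questions, the full length of the questionnaire. Every item therefore belongs to a course module, and the participant's eating is not an input.
4. The Abstract's sentence on repeating the T0 tools at T1 would supply the missing FS and diet measurements, but it conflicts with Table 1 and with both tool descriptions. The document does not say which governs.
5. The pictorial dietary assessment (PDAT) is repeated at T1 and does concern eating. It is not listed as a course measure, and at T1 it is taken under the modified menus, so it cannot separate the course from the menus.
6. The analysis section does not rank the course measures or say which one carries a conclusion about effectiveness.

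**The case against.** The strongest reply is that the knowledge questionnaire is not the only planned measure. The analysis section expressly includes FS and Mediterranean diet before and after the course, Principal Findings lists them as separate expected improvements, and one compressed sentence in an abstract should not override the methods. The body's secondary objective is feasibility and parents' knowledge, for which a questionnaire drawn from the course content is a reasonable instrument, and the Nutrition Knowledge section already limits it to what was learned. Ranking secondary measures may also properly be left to an analysis plan that is not shown.

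Much of this stands. A reader might infer that the plan judges the course by the questionnaire alone, or contains a rule under which a knowledge gain with no change in FS would be declared a success. The documents do not support either reading: FS is named among the measures, and no success rule is stated. Nor can one give a probability of such a declaration. The documents give no course attendance, no expected knowledge gain and no decision rule, and the power to detect an assumed true gain in knowledge would only show that a real gain can be detected.

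What the reply does not answer is the schedule. Naming FS as a pre/post measure does not help if its tools are used only at T0. That is a contradiction within the document, not a detail left to another one. The feasibility wording of the secondary objective, for its part, adds a further version of what the course is for.

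**Conclusion.** The point holds as a mismatch between goal, named measure and schedule. The course's goal is put as FS reduction in the Abstract and in the course description, the Abstract names a course-derived knowledge questionnaire to assess it, and of the three scores named for the pre/post comparison only knowledge is scheduled at both times. Followed as scheduled, a conclusion of effectiveness would rest on a measure that carries no information on FS.

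This rests on Table 1 and the two tool descriptions being what is followed. If the Abstract's sentence on repeating the tools at T1 is followed instead, an FS comparison exists, and what remains is the unranked list and the inconsistent objective. An FS score taken at T1 would, however, mix the course with the modified menus in a single-arm study. The point concerns a secondary objective and leaves the primary meal-acceptance comparison untouched. It should be corrected, because it decides what may be concluded about the course.

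**What to change.** 1. Reconcile the Abstract (Methods), Table 1, Food Habits, Feeding Behaviors During Mealtime, and Outcomes and Statistical Analysis. For the course subgroup, add BAMBI/STEP and KIDMED/MEDQS to the postcourse telephone interview already planned for the knowledge questionnaire, preferably before the modified menus start. Analyse each FS tool within its own age group (BAMBI 3-11 years, STEP 12-35 years), since they do not give one common score.
2. In the Abstract and the analysis section, base any claim about the course's effect on FS on the within-person change in FS, reported as an uncontrolled pre/post change. Label the knowledge score as knowledge acquisition and the dropout rate as feasibility.
3. Make the Abstract's objective and the Secondary Objectives section state the same aim.
4. If no postcourse FS data are collected, drop the claim of effectiveness on FS and report knowledge and feasibility only. The intervention phase was scheduled for April to June 2025, so this may already be the position.

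Rewording alone is not enough, because without a postcourse FS measurement there is nothing to analyse. The cost is a somewhat longer postcourse call: the T0 interview, which covered these tools and the sociodemographic form together, took 20 or 25 minutes, so the addition should be shorter than that. The other cost is that a claim of effectiveness on FS becomes harder to meet.

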**Results:**

Due to different timelines depending on the centers and schools involved, participant enrollment and data collection will take place at different times between Pavia, Milan, and Rome. In September 2024, enrollment was held in the Pavia and Milan care centers for a total of 74 participants enrolled. In Rome, the enrollment phase has not yet started; activities are expected to be carried out similar to those in Pavia and Milan.

**Conclusions:**

The AUT-MENU study is expected to yield significant insights and improvements in meal acceptance among individuals with ASD, particularly through the introduction of targeted menus in collective catering settings both in care centers and schools.

**Trial Registration:**

ClinicalTrials.gov NCT06266377; https://clinicaltrials.gov/study/NCT06266377

**International Registered Report Identifier (IRRID):**

DERR1-10.2196/57507

## Introduction

### Background

In recent years, the scientific community has placed particular emphasis on investigating and elucidating the feeding-related behaviors of individuals diagnosed with autism spectrum disorder (ASD). Research has highlighted the rituals related to mealtime that are frequently observed among this population [1].

Individuals with ASD commonly present various feeding challenges, including food refusal, limited food intake, and behavioral difficulties during mealtime [2,3], which results in imbalanced food habits [4]. These challenges fall under the umbrella term of food selectivity (FS), a term also referred to in the literature as “picky eating” and “fussy eating” [4]. Specifically, FS is characterized by the rejection of specific types of food, whether familiar or unfamiliar, often refusing more foods than they accept [5]. This selectivity may involve entire food groups, such as fruits and vegetables, or foods that share specific sensory characteristics, including taste, texture, or odor. When FS persists over time, the individual can be classified as “picky eater,” which may impact dietary variety and nutritional intake [5].

Valenzuela-Zamora et al [3] reported a prevalence of 23% to 69% for FS among a sample of 247 children with ASD aged 2-18 years compared with 267 children with neurotypical condition, where the prevalence ranges from 1% to 37%.

Specifically, individuals with ASD and FS tend to gravitate toward foods with soft or semiliquid textures, pale hues, mild flavors, homogeneity of hues within the same dish, and dishes containing ingredients of similar, noncontrasting color tones, while they show reluctance toward foods that are bitter, sour, or spicy. Additionally, they often avoid strong colors, strong odors, and high temperatures, leading to the exclusion of entire food groups [1,6] (eg, canned fish or vegetables such as broccoli and cauliflower). Moreover, individuals with ASD exhibit a notable preference for processed foods high in energy, simple sugars, saturated fats, and salt but deficient in essential minerals and vitamins [1]. Such preferences may contribute to an increased risk of becoming overweight or developing obesity and micronutrient deficiencies [2].

In certain instances, it is possible to pinpoint physiological factors that directly or indirectly contribute to these distinct feeding challenges, such as compromised sensory processing, issues in oral motor skills (chewing and swallowing), and gastrointestinal disorders [4]. Conversely, when identifiable organic factors are absent, FS may be interpreted as an expression of the restricted interests and behavioral inflexibility frequently linked with ASD [4].

The evolution of feeding challenges with age remains a subject of contention in the literature. In the systematic review by Page et al [7], 7 studies are included, exploring the relationship between age and feeding difficulties. Among these studies, only 3 indicate amelioration in eating challenges over time, regardless of interventions specifically addressing FS [7]. Specifically, these 3 studies followed a cross-sectional model. Beighley et al [8] found that FS, defined as “will eat only certain food,” decreased with increasing age. Gray et al [9] compared eating behaviors among children with ASD from childhood to adolescence and found that parents reported that picky eating decreased and eating a variety of foods increased from early childhood to adolescence. Finally, Bandini et al [10] found that food refusal declined with age, but there was no significant change in food repertoire over the 6-year period.

Considering what has been described so far, the delicate nature of mealtime for individuals with ASD is clear, and it highlights the challenges of managing FS attitudes both in domestic and collective catering settings. Acting in the household environment may present a crucial window of opportunity since family mealtime is described by most parents as stressful and frustrating. Moreover, parents or caregivers may unintentionally exacerbate meal-related anxiety and stress through nonfunctional attitudes [2,11-13]. Therefore, it is essential to provide caregivers with valuable information to address the challenges that arise during these moments. The organization “Autism Speaks” has released the document “Parent’s Guide to Feeding Behavior in Children With Autism” [14], suggesting simple strategies that can be easily implemented at the domestic level.

Collective catering is a critical setting too, as many adults with ASD consume their meals in the care centers where they reside, while children and adolescents have at least 1 meal a day at school. This setting opens a potential opportunity for intervention that, if properly exploited, can enable an improvement in the nutritional status of individuals with ASD through specifically formulated menus, leading to a cascade of beneficial effects on their health [1]. There are currently no specific guidelines about how to customize collective catering menus for participants with ASD in Italy. In fact, due to the specificity of the target population and the complexity of working with individuals affected by ASD, no multicenter studies aimed at improving food acceptance have so far been carried out on large groups across different age ranges.

The authors designed and conducted a pilot study, the FOOD-AUT project [6], in which canteen menus were adapted to meet the nutritional and sensory needs of adults with ASD, with the aim of reducing their FS and consequently improving their health. The study involved 22 participants and focused on adapting meals based on key sensory characteristics, such as texture, color, and shape, to enhance food acceptance. The results showed that personalized meal modifications could positively influence dietary variety and meal consumption in individuals with ASD. Since the pilot study was conducted in a single setting with a limited sample size, this study, the AUT-MENU project (improving the meal acceptance of participants with ASD), aims to extend the same model to multiple contexts, including care facilities and schools, to further evaluate its effectiveness. This broader implementation will strengthen the dataset and provide more robust evidence, ultimately supporting the development of specific dietary guidelines for collective catering services tailored to individuals with ASD.

### Study Objectives

#### Primary Objectives

The primary objective of the AUT-MENU project is to assess meal consumption among individuals with ASD in collective catering settings both quantitatively (eg, portion intake) and qualitatively (eg, sensory characteristics influencing food acceptance, such as texture, color, smell, and shape). Based on these findings and existing dietary guidelines for individuals with ASD [1,6], the project aims to improve meal acceptance by adapting the proposed meals accordingly.

#### Secondary Objectives

The secondary objective is to evaluate the feasibility of a structured nutrition and behavioral education program for parents and caregivers of enrolled participants. This intervention aims to improve parents’ knowledge on FS and meal experience at home, complementing the modifications implemented in the collective catering settings.

## Methods

### Study Overview

The AUT-MENU study is a single-arm pre- and postbicentric intervention study (without control). The study is conducted by a multidisciplinary team consisting of researchers from the Laboratory of Dietetics and Clinical Nutrition of the University of Pavia and the Research Centre for Food and Nutrition of Rome.

### Setting

#### Overview

The study is being conducted in 2 different regions of Italy. In the northern region, 3 care centers have been involved: Tiglio Fondazione Onlus in Pavia, Dosso Verde in Milan, and Dosso Verde in Pavia. In the central region, the study is taking place in 1 high school in Rome: the “Giuseppe Garibaldi” Agricultural Technical Institute.

#### Tiglio Fondazione Onlus

Fondazione Tiglio is a nonprofit organization active since 2004. The center offers a range of residential and nonresidential services specifically designed for young adults or adults (≥18 years) with severe or profound intellectual, physical, and sensory disabilities as well as neurodevelopmental disorders (eg, autism). These services include educational, assistive, socio-health care support, work training, and recreational-cultural activities. The facility also provides an external catering service that offers a complete lunch for the users.

